### SLIM intervention

The core components of the SLIM intervention are *health technology*, *motivational interviewing*, *feedback and goal setting*. Health technology includes the Oura-ring, an electronic food diary and a SLIM application. The Oura ring is a commercial wearable ring that captures various health parameters and provides various daily scores for the user. The ring–equipped with different biosensors including a built-in photoplethysmography (PPG) sensor and an inertial measurement unit (IMU)–provides heart rate, nocturnal heart rate variability, nocturnal respiration rate, sleep duration, body temperature, and step counts. The ring is water resistant, lightweight and easy to use for short-term and long-term monitoring. The ring’s battery allows up to one-week data collection per charge. The collected data are transferred to the Oura mobile app (iOS or Android) via Bluetooth and then to the cloud server [31]. Participants wear the Oura rings continuously starting from gestational week 15 or less and continue until the postnatal visit 12 weeks after delivery. The electronic food diary, FatSecret is a free of charge, online diet, nutrition and weight loss service that allows users to set up unique user profiles, track their activity, food intake and weight. The services offered by FatSecret include the FatSecret websites and mobile applications [32]. Participants complete a food diary for one week at three timepoints: gestational week 15 or less, gestational week 34 and eight weeks after the delivery. The SLIM application is a platform that enables researchers to send e.g. questionnaires and surveys to participants. PHNs utilize the data monitored and collected with the Oura smart ring and the food diary during routine maternity care visits to evaluate physical activity, sleep and nutrition. PHNs give feedback to the women based on the data. They use motivational interviewing focusing on helping individuals to identify and resolve any ambivalence about changing behavior [33], and create goals in collaboration with women. The goals are documented in patient records. Participants are asked to answer questionnaires at three timepoints: gestational week 15 or less, gestational week 34 and 12 weeks after the delivery.

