## Introduction

Obesity has nearly tripled during the last few decades [1] and has become a global health concern; this trend can also be seen among pregnant women. In Finland, for example, 41.7% of pregnant women were overweight (BMI ≥25) and 17.6% were obese (BMI ≥30) in 2019 [2]. Correspondingly, almost a third (29%) of pregnant women in the US were obese in 2019 [3]. Maternal overweight increases the risks for obstetric complications and newborn mortality and morbidity, such as gestational diabetes, obstetric intrapartum complications, and caesarean section, macrosomia and stillbirths [2, 4, 5]. Consequently, preventing and decreasing obesity in pregnant women is essential to improve the health of future generations. Pregnancy is an exceptional period in a women’s life; there is often a shift in attitude and a spontaneous change in positive health behaviors, making women more receptive to advice on nutrition and physical activity. It is crucial to support their willingness to change health behaviors and encourage the motivation to take care of their own and their unborn child´s health. Healthy lifestyle behaviors adopted during pregnancy are also likely to have positive impacts on women’s health after pregnancy [6].

Previous behavioral lifestyle interventions focusing on a healthy diet and physical activity have succeeded in reducing gestational weight gain and improving pregnancy outcomes, for example, by reducing the number of macrosomia or caesarean sections. Further, some interventions have reduced neonatal respiratory distress syndrome and some interventions have also been associated with a reduction of postnatal depression [7–10]. However, these interventions have focused on single outcomes, and are not established as part of maternity care. In addition, counseling that focuses on giving general information on healthy diets and exercise is not usually effective; instead, the focus should be placed on individual barriers and challenges. Furthermore, weight gain may not be the most optimal parameter to focus on during pregnancy because obesity is a sensitive and stigmatizing subject, which is often found to be difficult to discuss with pregnant women. Hence, the focus of interventions should be on health promotion instead of weight loss [11]. Overall, there is a clear necessity for innovative and cost-effective lifestyle interventions to promote weight-management and health outcomes [8, 12].

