**Step 3**: Development and selection of strategies and measures for practicing change were conducted by linking identified target behaviors and determinants of the national guidelines to the intervention components. Previously identified weight management target behaviors [28] were mapped to the matrix of BCW (S1 Table). These results were presented to the PHNs and based on their discussions and consensus the most helpful elements for their clinical work in maternity clinics were chosen. These elements were *health technology* to support self-monitoring and goal setting, *motivational interviewing*, *feedback and goal setting* to enhance the motivation to improve self-efficacy in weight-management. A template for the intervention description and replication (TIDieR) was used as a guideline to improve the comprehensive reporting of the intervention (S2 Table).

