#### Well-being data

*Data on dietary intake* that is collected with the mobile app (FatSecret), and the nutritional intake (Calories, Protein, Fat and Carbohydrate) are both included in analysis. The app also displays the data by meal and snack eaten to observe meal patterns. FatSecret has been shown to be accurate and practical [52]. The outcome variable of interest in this study is the total kilocalories per day.

*Data on activity*, *sleep and stress* is collected with the Oura-ring. Studies in the literature have indicated the reliability of the ring in terms of sleep, physical activity, heart rate, and heart rate activity [53–55].

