#### Data analysis

The data will be analyzed statistically. Appropriate descriptive statistics will be calculated for the background variables, WEL, PASE, weight change, EPDS, WHOQOL-BREF, PRAQ-R2, PSS-4, SOC-13, TFEQ-R18, 6-FQ, calories consumed, and the Ouras parameters. Variables like the EPDS, baseline BMI and Ouras wear time will be tested for their association with changes in self-efficacy in eating and physical activity. Mixed effect models will be used to evaluate change over time in self-efficacy in eating and physical activity and weight change. Simple mediation models will be used to assess calories consumed and MVPA as mediators between self-efficacy and weight change.

Machine learning and event mining approaches are being exploited in the intervention to build personal models–such as sleep and physical activity–for each individual. The relationships between the collected parameters, including weight gain, physical activity, sleep, and stress will also be investigated. Signal processing and (for example, unsupervised and semi-supervised) machine learning techniques are being exploited to extract events–i.e., high abstraction level information–from the data collected via the Oura ring and the questionnaires. These events characterize pregnant women’s daily life or lifestyle: e.g., their physical activity during the day or stress levels during sleep and these events are defined based on different attributes in certain epochs varying from minutes to a day. The events will be divided into three categories: activity, health, and context. Subsequently, the relationships between the events and their attitudes will be investigated via statistical analysis techniques. For example, when an undesired event (e.g., stress) is detected during pregnancy, statistical analysis techniques (e.g., Chi-Square test) will be used to evaluate the relationships between the event and the mother’s activity, health, and context. Moreover, higher data abstraction will be performed to record events in a chronological order. Data analytic techniques ranging from simple rule-based algorithms to machine learning classifications will be developed to extract patterns from the collected data and events. To this end, machine-learning-based methods (e.g., autoencoders) will be developed to build personalized models, by which the pregnant woman’s real state is compared with the desired state.

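### The food diary is both an intervention tool and the only source of calories consumed, so the calorie mediation cannot separate less logging from less eating

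*Protocol article*

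**What the plan says.** All references are to the protocol article.

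- **The diary as intervention.** The section on the SLIM intervention states "Health technology includes the Oura-ring, an electronic food diary and a SLIM application", and this technology is one of the core components. Step 3 of the development section gives its purpose as "to support self-monitoring and goal setting". On use at visits the text says "PHNs utilize the data monitored and collected with the Oura smart ring and the food diary during routine maternity care visits", followed by "PHNs give feedback to the women based on the data". The nurses also "create goals in collaboration with women. The goals are documented in patient records".
- **The schedule.** The diary is kept for one week at each of three times: gestational week 15 or less, week 34, and eight weeks after delivery.
- **The diary as measurement.** Under Well-being data, dietary intake comes from the same app, and "The outcome variable of interest in this study is the total kilocalories per day". Under Data analysis, calories consumed are listed for descriptive statistics, and "Simple mediation models will be used to assess calories consumed and MVPA as mediators between self-efficacy and weight change".
- **The setting.** Design and settings describes a non-randomized pre-post trial, and no control group is described. The Introduction remarks that "obesity is a sensitive and stigmatizing subject".
- **Checks named.** Ring wear time is named as a covariate and as a fidelity measure, and missing data are assessed for questionnaires. Neither check names the diary. The one assurance on the diary is a citation for the app's accuracy and practicality.

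**The concern.** One self-entered record does two jobs. It is what the nurse works from with the woman, and it is the measurement from which the mechanism of the intervention is to be inferred. The later diaries are kept after feedback and goal setting, so the share of true intake that gets logged may differ from the first diary because of the intervention itself. A constant logged share would give no false percentage change; a share that changes with exposure would. With no comparison group described and no second measure of intake, nothing in the article tells the two explanations apart.

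At stake is the statement that self-efficacy acts on weight through calories. It can be wrong in either direction:

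- If women who gain more self-efficacy also log less, a path from self-efficacy to calories appears without any change in eating.
- If logging varies for unrelated reasons, the calories-to-weight slope is diluted and a real path may be missed.

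**Working it through.** The plan states no figure on this point, so there is nothing to reproduce. The dual role follows from reading the sections above together. The arithmetic below shows direction and scale only. Apart from the 54 women and the 20% loss, every input is an assumption and none comes from the article.

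**1. Apparent fall in calories with unchanged eating.** Assume a true intake of 2,200 kcal/day throughout and a first logged share of 90%.

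- First diary: 2,200 × 0.90 = 1,980 kcal/day.
- Later share 90%: no apparent fall.
- Later share 85%: 2,200 × 0.85 = 1,870, a fall of 110 kcal/day (110/1,980 = 5.6%).
- Later share 80%: 2,200 × 0.80 = 1,760, a fall of 220 kcal/day (220/1,980 = 11.1%).

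**2. Chance of declaring a self-efficacy-to-calories path from logging alone.** Completers: 54 × 0.80 = 43.2, taken as 43. With Fisher's z, the approximate power is P(Z > 1.96 − atanh(r) × √(n − 3)), two-sided 5%, with √40 = 6.325.

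- r = 0: 5%, the nominal level.
- r = 0.2: 0.2027 × 6.325 = 1.282, power 0.25.
- r = 0.3: 0.3095 × 6.325 = 1.958, power 0.50.

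These probabilities concern that single path. They are not false-positive rates for the indirect effect.

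**3. Effect on the mediation estimate.** Logged calories were modelled as true calories plus a logging error, in 200,000 simulated records. Assumptions: true calories affect weight by 0.004 kg per kcal; true calories have SD 400 kcal; the logging error has residual SD 200 kcal; self-efficacy has a direct effect of −0.3 kg per SD and no effect on true intake.

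The calories-to-weight slope shrinks by 400²/(400² + 200²) = 160,000/200,000 = 0.8, that is 0.004 × 0.8 = 0.0032. The indirect effect is the self-efficacy-to-logged-calories slope times 0.0032:

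| Change in logging per SD of self-efficacy gain | Expected indirect effect (true value 0) | Simulated indirect effect | Simulated direct effect (true −0.3) |
|---|---|---|---|
| 0 kcal | 0 | −0.002 kg | −0.30 kg |
| −100 kcal | −100 × 0.0032 = −0.32 kg | −0.318 kg | +0.02 kg |
| −200 kcal | −200 × 0.0032 = −0.64 kg | −0.638 kg | +0.34 kg |

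The first row matters as much as the others: logging error unrelated to self-efficacy creates no false indirect effect. It only dilutes a real one. With a true self-efficacy effect of −100 kcal and unrelated logging error, the simulation gave −0.324 kg where the true value was −0.4 kg.

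**The case against.** The case on the other side is substantial.

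- **Calories are not an effectiveness endpoint.** The primary outcomes are the two self-efficacy scales and the secondary outcome is weight gain. Mixed models are named for those only. Calories are described and used as a mediator, and the sentence calling kilocalories the outcome variable of interest can be read as choosing among the nutrients the app records. This stands. A reader might infer that a fall in logged calories will be tested and reported as a change in intake, but no such test or claim is planned.
- **Growing under-logging is not shown.** The first diary already belongs to the intervention and the procedures are explained beforehand, so awareness of nurse review may exist from the start. This stands: it is a risk of unknown size, and zero is within the range.
- **The nurse's role is easily overdrawn.** A reader might infer that the nurse checks the diary against agreed goals. The text says that nurses evaluate nutrition, give feedback and create goals, using motivational interviewing. The remark on stigma concerns obesity and why weight gain may be a poor focus; it says nothing about food logging.
- **False mediation needs a further assumption.** Logging must change with self-efficacy, and no statement in the article supports that. This also stands, and the zero row of the table confirms it.
- **Completeness rules belong in a fuller plan.** Their absence from an article is indeed no defect. But the dual use of the diary and the label of calories consumed are fixed in the article itself, and those are what limit the conclusion.

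**Conclusion.** The point holds as a limit on interpretation. The diary is an intervention tool and the only stated source of calories, and with no control group described the planned mediation cannot distinguish mediation through eating from mediation through logging. The direction of the error depends on whether logging changes with self-efficacy: if so, a false path can arise; if not, a real path is weakened.

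The size is unknown. The 110 to 220 kcal/day, the probabilities of 0.25 and 0.50, and the indirect effects of −0.32 and −0.64 kg all rest on assumed values and show only that modest logging changes could matter. A reader might take the 25 to 50% as the chance of falsely declaring mediation; it is not, because it applies to the self-efficacy-to-calories path alone and presupposes a correlation caused by logging.

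The severity is minor. The self-efficacy and weight analyses do not use the diary, and the mediation is not a primary or secondary outcome analysis.

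**What to change.** Under Well-being data and Data analysis:

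1. Define the variable and the mediator as logged intake.
2. Report logged days and logged meals per diary week at each of the three time points.
3. Set a completeness limit for a diary week in advance, and repeat both the calorie description and the calorie mediation using only weeks that meet it.
4. If an energy-plausibility flag is added, base it on early-pregnancy weight and allow for pregnancy stage and lactation. A flag using concurrent weight would tie exclusion to the weight outcome. A flag that ignores pregnancy stage and lactation could change between time points for physiological reasons. Such a flag may also miss a drift of 5 to 10 percentage points in the logged share, so it should supplement the completeness rule and not replace it.
5. State any positive result as mediation through logged intake, and only if both analyses agree. Note that selective under-logging within complete weeks cannot be excluded.

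The cost is small: one additional analysis on data already being collected, with no change to visits or to the intervention. The sensitivity analysis will include fewer women and have a wider interval, so agreement may be harder to show.

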### Evaluation of the effectiveness of the SLIM Intervention

#### Data collection

In the initial antenatal appointment, the PHNs provide a letter of information and ask permission for the researchers to be in contact with the potential participants. The researchers then explain the study purpose and procedures to the women in a scheduled appointment. In addition, an Oura ring, and instructions on how to use it and other applications are given to each participant by the researchers after informed consent.

#### Outcome measures

The primary outcomes for the effectiveness of the intervention are self-efficacy in eating and physical activity and reduced weight gain during pregnancy (secondary outcome). To track variations and trends, health parameters are collected, these include: weight retention postpartum, depressive symptoms, quality of life, pregnancy specific anxiety, perceived stress, sense of coherence, eating behavior and lifestyle patterns, physical activity levels, sleep quality, stress levels and dietary intake. (Fig 1).

#### Measurements

Participants complete the questionnaires via the SLIM application at recruitment (<15 pregnancy week), at 34 gestational weeks and 12 weeks after delivery.

#### Primary outcomes

Eating self-efficacy and physical activity self-efficacy are measured with following questionnaires:

**Weight Efficacy Life-Style Questionnaire (WEL)**: is a standard, validated and clinically meaningful measure of eating self-efficacy. WEL consists of 20 items, which are scored on a Likert-type scale from 0 to 9 (0: Not confident, 9: Very confident). Answers are assembled into five factors (four questions for each factor): confidence in being able to resist the desire to eat in the following contexts: negative emotions, availability, social pressure, physical discomfort and positive activities. The eating self-efficacy score is calculated by adding together all 20 items. A level of eating self-efficacy is defined by a high score on the WEL questionnaire [34, 35]. The validation studies reported an internal consistency for Cronbach’s α of 0.70–0.90 in overweight Caucasian population.

**Self-Efficacy for Physical Activity Scale (PASE)** is a valid questionnaire to assess confidence in the ability to exercise when faced with specific barriers. It has been modified for pregnant women. Participants are asked to rate their confidence in engaging in physical activity across a variety of situations. Responses are measured on a Likert scale ranging from 1 to 5 (1 = *not at all confident*, 5 = *extremely confident*). The PASE score is calculated by taking the sum of the 5 items. The internal consistency for Cronbach’s α was between 0.70–0.78 in a Latino women sample [36, 37].

#### Secondary outcome

**Weight gain** is measured by PHNs at every antenatal appointment, on average eight times. The women’s weight before delivery is then compared to the national recommendations based on their BMI before pregnancy. For those women whose pre-pregnancy BMI is 25–29.9, the recommended weight gain during pregnancy is 7–11 kg and for those women whose pre-pregnancy BMI is 30 or more, a gain 5–9 kg weight during pregnancy is recommended [38].

#### Health parameters

**Edinburgh Postnatal Depression Scale (EPDS)** is a reliable and valid 10-item questionnaire that screens women for symptoms of emotional distress during pregnancy and the postnatal period. The total score is calculated by adding the numbers selected for each of the 10 items. Depression is defined by a high score on the EPDS. Cut-off scores range from 9–10 to 13–14 [39, 40]. In this study, a cut-off score ≥10 has been used to indicate possible depression. The reliability values of the Edinburgh Depression Scale indicated by Cronbach’s *α* coefficient per trimester were 0.82, 0.83, and 0.84, respectively among an unselected sample of 845 pregnant women [41, 42].

**WHOQOL-BREF** is a well-accepted, valid generic 26-item instrument and the mostly commonly used instrument to assess quality of life. Responses to questions are measures on a 1–5 Likert scale where 1 represents "disagree" or "not at all" and 5 represents "completely agree" or "extremely”. WHOQOL-BREF has four domains: Physical health, psychological health, social relationships and environment. The score is calculated by adding together the point values for the questions corresponding to each domain and then transforming the scores to a 0-100-point interval. The first two questions on the WHOQOL-BREF do not correspond to a domain, but are meant to provide a global assessment of quality of life. Higher scores in each of the domains correspond to a greater perceived quality of life. The internal consistency measured by Cronbach’s alpha ranged from 0.71 to 0.77 in the sample of 190 postpartum women [43, 44].

**PRAQ-R2** is a valid pregnancy-specific anxiety questionnaire. Responses are measured with a Likert type scale ranging from 1 (definitely not true) to 5 (definitely true). The items in the PRAQ-R2 can be ordered into three subscales: Fear of giving birth, worries about bearing a physically or mentally handicapped child and concern about one’s own appearance. Cronbach’s alphas across the total scale were good (above 0.80) in a sample of Finnish pregnant women (n = 1152) [45].

**Perceived Stress Scale (PSS-4)** is a validated measure which rates on a 5-point scale the extent to which participants have experience stress-related symptoms in the past month. Responses are measured with a Likert type scale ranging from 0 (never) to 4 (very often), the Cronbach’s α = 0.77 (English sample). Higher values indicate more stress [46, 47].

**Sense of Coherence (SOC-13)**: is measured with a 13-item SOC questionnaire, which has three subscales: Meaningfulness (4 items), Comprehensibility (5 items), and Manageability (4 items). Responses are scored on a 7-category semantic differential scale with two anchoring responses tailored to the content of each item. Five items (1, 2, 3, 5, and 7) are reversed before adding together the scores to obtain the total score. The total score can range from 13 to 91 and a higher score indicates a higher SOC. The internal consistency measured by Cronbach’s alpha ranged from 0.70 to 0.92 [48]. The sense of coherence scale shows high internal consistency [49].

**The three-factor eating questionnaire (TFEQ-R18)** is used to measure eating behavior tendencies [50], which has three domains: cognitive restraint (6 items), uncontrolled eating (9 items) and emotional eating (3 items). Responses are measured on a 4-point Likert scale, except for one item using an 8-point Likert scale. The range of total scores are from 0–100. To calculate the scores of the subscales, items 1–13 are reverse-coded, so that higher scores indicate a higher level of eating behavior tendencies. Cronbach’s alphas for the three domains were 0.71, 0.88 and 0.89 respectively (Swedish sample).

**6-FQ is** a 27-item self-administered instrument with psychometric properties that measures lifestyle pattern factors: Convenient Diner, Fast Pacer, Easily Enticed Eater, Exercise Struggler, Self-Critic and All-or-Nothing-Doer. Responses are measured on a 4-point Likert scale: “don’t agree at all” (0), “agree a little” (1), “agree” (2) and “strongly agree” (3). The score range is from 0–81, and a higher score indicates unhealthy lifestyle pattern factors. The Cronbach’s reliability estimates for internal consistency ranged from 0.76 to 0.85 (sample of overweight or obese adults) [51].

**Background information questionnaire**: The maternal background characteristics including age, BMI, marital status, education and employment status are collected with a self-administered background information questionnaire.

